**Adverse effects and list of complaints (LC)**

The LC consists of 66 items, yielding a global score measuring physical and general discomfort [88]. The LC list is administered at the beginning and at the end of the session with reference to complaints throughout the entire session. Subjects will also be asked to report any adverse events during the sessions or between study sessions at the beginning of the next session. The test requires about 2 minutes.

**State-Trait Anxiety Inventory (STAI - G) and STAI (STAI- S)**

This is a questionnaire given to adults to determine the general anxiety levels. Based on responses to 20 items, with scores ranging from 1 (“almost never”) to 4 (“almost always”), a total score is calculated. The total Trait scores range from 20 to 80, with higher scores indicating more pronounced anxiety and scores. A score above 45/80 indicating clinically significant anxiety symptoms. The State Anxiety Scale (S-Anxiety/STAI-S) evaluates the current state of anxiety, asking how respondents feel “right now,” using items that measure subjective feelings of apprehension, tension, nervousness, worry, and activation/arousal of the autonomic nervous system. The Trait Anxiety Scale (T-Anxiety/STAI-G) evaluates relatively stable aspects of “anxiety proneness,” including general states of calmness, confidence, and security [58]. We will use the STAI-G for the screening and the STAI-S for the main visits. The test requires about 5 minutes.

**Short form 36 Health survey (SF 36)**

The SF 36 is a self-reported measure of health status with 36 items which assesses eight multi-item variables: Physical functioning (10 items), social functioning (2 items), role limitations due to emotional problems (3 items), mental health (5 items) energy and vitality (4 items), pain (2 items) and general perception of health (5 items) [59]. The subjects will be asked to fill out the form at the screening visit. The questionnaire requires about 5 minutes.

**Toronto Alexithymia Scale 20 (TAS 20)**

Alexithymia is described as a trait to identify and describe emotions experienced by oneself or others. It is characterized by a marked difficulty in consciously experiencing, identifying, and describing emotions, as well as reduced introspection. The TAS 20 has a three-factor structure: difficulty identifying feelings, difficulty describing feelings and externally oriented thinking. It includes 20 questions with scores ranging from 1 (strongly disagree) to 5 (strongly agree) [59, 60]. We will use the TAS 20 as a baseline evaluation at the screening visit. The questionnaire requires about 2 minutes.

### **Beck's Depression Inventory II (BDI II)**

The BDI II is one of the most used self-reported scales for measuring depression. It uses 21 items ranked from 0 (symptom absent) to 3 (severe symptoms) to measure the severity of depression. The self-administered form takes about 5-10 minutes for the participant. The minimum score is 0 and maximum score is 63. In non-clinical populations, scores above 20 indicate depression. In those diagnosed with depression, scores of 0–13 indicate minimal depression, 14–19 (mild depression), 20–28 (moderate depression) and 29–63 (severe depression) [61, 62]. We will use the BDI II as a baseline evaluation of depression at the screening visit. The questionnaire requires about 5 minutes.

### **Subjective effects questionnaire (Visual Analog Scales, VAS)**

VAS will be repeatedly used to assess subjective alterations in consciousness over time. VAS will be presented as a range from 0 to 10 marked with “not at all” on the left and “extremely” on the right [38, 42, 63]. The following VAS will be used: “any effect”, “good effect”, “bad effect”, “liking”, “high”, “happy”, “fear”, “stimulated”, “feeling close to others”, “concentration”, “thinking”, “open”, “trust”, “want to be with other people”, “loss of sense of time”, and “the boundaries between myself and my surroundings seemed to blur”. Scales will be administered before and repeatedly after substance administration and will take 2 minutes to answer. The maximal ratings ( $E_{\max}$ , 0-10) are defined for each VAS and  $E_{\max}$  values compared between treatments using analysis of variance (ANOVAs).

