#### 4.3.2. Main visit (MDMA or placebo)

During the main visits, participants will present in the morning at the study site. An indwelling intravenous catheter will be placed in an antecubital vein for blood sampling. To avoid clotting participants will receive continuous 0,9% NaCl infusion during the whole visit with a total of maximum of 250 ml (40 ml/h). Patients with central diabetes insipidus and secondary adrenal insufficiency on hydrocortisone (HCT) substitution will be asked to take 50 mg HCT instead of the regular dose for the main visits (30mg morning dose and 20mg noon dose), desmopressin will be taken by the patients as regular.

Pregnancy test /drug screening: The participants will be screened for pregnancy and illicit drugs using a urinary test before starting the session at each visit. Positive screens for stimulants, opioids or tranquilizers will result in exclusion from the study. Positive screens for THC (cannabis) will be recorded but do not result in study exclusion. This is because THC consumption can be detected in urine for up to several weeks and use days before a study day is unlikely to affect the outcome.

Questionnaires: A standardized list of complaints (LC) (see further information below) and the STAI-S will be performed on baseline (timepoint 0min) and repeated at timepoint 180min (STAI-S), timepoint 360min (LC).

Vital parameters: Blood pressure (systolic and diastolic), heart rate and body temperature will be measured at several timepoints during the main visit (timepoint -60 min, 0 min, 30min, 60 min, 90 min, 120 min, 150min, 180min, 210min, 240 min, 270min, 300 min, 330min, 360 min).

Study Drug: MDMA (100mg) or placebo will be administered orally one hours after the start of the main visit.

Subjective effects: Autonomic and subjective/emotional effects will be assessed repeatedly throughout the main visit (timepoint 0 min, 30min, 60 min, 90 min, 120 min, 150min, 180min, 240 min, 300 min, 360 min) using subjective effects questionnaire assessed with visual analog scales (VAS).

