#### **4.3.3. Telephone interview**

Based on previous studies experience no formal follow-up support is needed but we will perform a telephone interview. 3 days after the main visits, patient or healthy participant will receive a phone call to inquire for Adverse Events using:

- A. The List of complaints e.g. sleeping problems, dry mouth, dizziness, palpitation, tremor, nausea, headache, transient anxiety and concentrating difficulties.
- B. Adverse Events that are not recorded by the LC e.g. subjective signs of depressed mood, psychosomatic problems, psychological problems and any perceptual disturbance e.g. flash backs.

The schedule of events for a subject is shown on **table1**

|                                         |                                          | SCREENING
VISIT | VISIT 1
MDMA/PLACEBO | VISIT 2
MDMA/PLACEBO | TELEPHONE
INTERVIEW
1 and 2 |
|-----------------------------------------|------------------------------------------|--------------------|-------------------------|-------------------------|-----------------------------------|
| Informed consent & Eligibility criteria |                                          | x                  |                         |                         |                                   |
| Questionnaires / Examination     |                                          |                    |                         |                         |                                   |
| Medical history questionnaire           |                                          | x                  |                         |                         |                                   |
| General physical examination            |                                          | x                  |                         |                         |                                   |
| ECG / standardized blood pressure       |                                          | x                  |                         |                         |                                   |
| Psychiatric interview (DSM IV)          |                                          | x                  |                         |                         |                                   |
| Questionnaires                          | Short Form 36 Health Survey (SF 36)      | x                  |                         |                         |                                   |

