Recreational use of Ecstasy has been linked to reversible neurotoxicity [78, 79], especially when the drug is taken frequently and in high doses [80]. In contrast, imaging studies do not indicate any changes after moderate MDMA use [35]. Several studies document no lasting effects of Ecstasy in moderate Ecstasy users [53, 78, 81]. No changes in serotonin transporter density were seen using positron emission tomography and [11C]-McN5652 four weeks after MDMA

administration (1.5-1.7 mg/kg) in MDMA-naive human volunteers [86,87]. The use of MDMA in controlled settings is considered safe with regard to neurotoxic effects [47, 82].

MDMA has rarely been associated with liver toxicity but often under overdose and not in controlled clinical setting [56]. Liver enzymes will be measured at the screening visit and pathological results will be excluded regarding the exclusion criteria.

The participants will be under continuous medical supervision and closely monitored during MDMA application and until the acute effects completely subsided; expected within 6h for MDMA [74]. Subjects with known risk factors for future drug abuse including current major depression, psychotic disorder and anxiety disorders [83] and prior drug dependence or other relevant illicit drug use [84] will be excluded from the study. Illicit drug use will also be monitored during the study using repeated urine drug screens before both main sessions.

Six hours after stimulation participants will be allowed to return to their home alone. If effects persist, the night is spent at the research facility. In the case of unexpected prolonged or severe adverse reactions subjects will remain in the hospital and are monitored as long as necessary. Subjects will be provided with the phone number of the study physicians in case of an emergency between/after study sessions.

MDMA is expected to produce sequelae (1-3 days post MDMA) including difficulty concentrating, irritability, or slightly depressed mood in about 10% of subjects [69]. Participants will receive a phone call 3 days after the intervention to assess mood changes and adverse events.

MDMA is neither mutagenic nor teratogenic and their chronic use is not associated with birth defects. Pregnant women are excluded from the study and pregnancy tests will be done before each test session. Effective birth control will be mandatory for female participants.

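### The session maximum (Emax) is the only VAS summary, so it cannot measure a transient fall in 'concentration' or 'thinking' if these items start above zero

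*Protocol*

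**What the plan says.** The VAS part of Protocol section 4.3.2 uses one format for every item: "VAS will be presented as a range from 0 to 10 marked with “not at all” on the left and “extremely” on the right". Sixteen items are listed, among them *concentration* and *thinking*, each as a bare label with no full wording and no expected direction. On timing it says "Scales will be administered before and repeatedly after substance administration", and the main-visit text gives the schedule as "timepoint 0 min, 30min, 60 min, 90 min, 120 min, 150min, 180min, 240 min, 300 min, 360 min".

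The summary is fixed for all items alike: "The maximal ratings ( $E_{\max}$ , 0-10) are defined for each VAS". The Emax values are then "values compared between treatments using analysis of variance (ANOVAs". The section does not say whether the 0-min rating counts towards Emax. It defines no minimum, no change from predose and no area under the effect curve.

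Section 5.1 leaves the remaining secondary endpoints to description. The time courses it names are those of oxytocin, MDMA and the other hormones, not the VAS. Section 3.4 expects peak effects after 2 h and a duration of about 6 h. Subjective effects are secondary endpoint E in section 3.2, and the matching objective in section 3.1 is worded as a change in subjective feelings.

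**The concern.** A maximum suits an item that starts near zero and can only rise, such as *any effect*, *high* or *bad effect*. It does not suit an item that a sober person rates well above zero and that the drug might lower. For such an item the highest rating of the session is the one taken before the effect starts or after it has gone. The same level is found on the placebo day, so the two maxima are nearly equal.

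If *concentration* and *thinking* are of this kind, a small Emax difference says little about whether they were impaired or by how much. A reader could still take it as evidence of no impairment, although the measure could hardly have shown any. The 0-min rating and all later ratings are collected, but the stated summary makes no separate use of them.

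**Working it through.** The protocol gives no figure to reproduce here. The check has a deterministic part and a simulated part.

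**Inputs from the protocol.** Ten rating times from 0 to 360 min (section 4.3.2); peak at 2 h and duration of about 6 h (section 3.4); 0-10 scale; 15 persons per group, 30 in total (synopsis; section 5.2 also gives 30).

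**Assumed inputs, not in the protocol.** Sober level 6. True fall of D = 2 or 4 points that starts after 30 min, is largest at 120 min and is gone by 360 min, linear on both sides. No change on placebo.

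**Step 1, no rating noise.** The fraction of the fall present at time t is (t - 30)/90 from 30 to 120 min and (360 - t)/240 after that, and it is 0 at 0 min. The rating is 6 minus D times this fraction.

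| min | 0 | 30 | 60 | 90 | 120 | 150 | 180 | 240 | 300 | 360 |
|---|---|---|---|---|---|---|---|---|---|---|
| placebo | 6 | 6 | 6 | 6 | 6 | 6 | 6 | 6 | 6 | 6 |
| D = 2 | 6 | 6 | 5.33 | 4.67 | 4 | 4.25 | 4.5 | 5 | 5.5 | 6 |
| D = 4 | 6 | 6 | 4.67 | 3.33 | 2 | 2.5 | 3 | 4 | 5 | 6 |

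- Emax, MDMA minus placebo: 6 - 6 = 0 for both falls, with or without the 0-min rating.
- Emin, MDMA minus placebo: 4 - 6 = -2 and 2 - 6 = -4.

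If the 0-min rating counts, Emax cannot be below the predose rating, whatever follows. If it does not count, the 30-min and 360-min ratings lie at the edges of the effect and give the same result here.

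**Step 2, with noise.** Further assumptions: person-to-person SD 1; shift of the sober level between visits, SD 0.5 to 1.0; rating noise, SD 0.3 to 1.0; ratings limited to 0-10; 0-min rating counted; 4000 runs per setting. The test is a paired t-test at 0.05, which equals the two-treatment within-subject ANOVA.

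| Measure | Fall of 2 | Fall of 4 | Significant, 15 persons | Significant, 30 persons |
|---|---|---|---|---|
| Emax difference | -0.20 to -0.50 | -0.21 to -0.63 | 8-51% | 11-83% |
| Emin difference | about -1.3 to -1.6 | about -2.8 to -3.5 | 78-100% | 98-100% |

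Doubling the fall hardly moves Emax. The small negative value arises because fewer ratings stay near the sober level on MDMA, so the highest of the noisy ratings is slightly lower. It reflects rating noise more than the drug effect.

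**Step 3, subtracting the 0-min rating.** That rating is taken before the effect starts, so its expected value is the same on both days. Subtracting it leaves the mean differences in the table unchanged and adds the noise of one rating.

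**Step 4, a rise.** A simulated rise of 4 points from a level of 5 gave an Emax difference of +3.2. Emax therefore works for items that go up.

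**The case against.** **The protocol does not predict a fall during the session.** A reader might infer that it does, because it says "MDMA is expected to produce sequelae (1-3 days post MDMA) including difficulty concentrating" and lists "transient anxiety and concentrating difficulties". The first statement (section 7.2) concerns the days after dosing and about 10% of subjects. The second (section 4.3.3) belongs to the telephone call three days later. The VAS stop at 360 min. The common acute effects in section 7.2 do not include concentration, and the same section reports no indication of adverse cognitive effects in controlled settings. Nothing is said about *thinking*. This objection stands and makes the point conditional.

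**The item wording is not shown.** If *concentration* asks how altered it is, a sober rating is near zero and Emax is suitable. The document does not settle this.

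**A wider reading does not hold.** One might argue that a person's usual level distorts Emax for *happy*, *open*, *trust* and *want to be with other people*. The protocol compares Emax between treatments in a crossover, so a stable personal level is present on both days and largely cancels, apart from ceiling effects. It specifies no raw comparison of Emax between patients and controls.

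**Saying that a fall would be missed is too strong.** With no shift in sober level between visits, the small Emax difference reaches significance in about 54-90% of runs with 15 persons and 86-99.7% with 30. Its size still hardly depends on the fall. The List of Complaints, which covers the whole session and includes concentrating difficulties, would also catch part of such an effect.

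**The statistical analysis plan may refine VAS scoring.** It may, but the protocol does not leave the summary open: it fixes Emax for every item.

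**Conclusion.** The point holds in conditional form. If *concentration* and *thinking* are rated as abilities with a non-zero sober level, and if they fall on MDMA and recover within the session, Emax does not measure the fall. Its difference is about -0.2 to -0.6 for true falls of 2 to 4 points.

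The principle is arithmetic. The magnitudes rest on an assumed sober level, time course and noise, none of which the protocol gives. The documents do not show that a fall will occur, do not support extending the point to the items with a personal level, and do not make Emax wrong for items that start near zero. What is affected is two of 16 items within one secondary endpoint. The primary endpoint is untouched.

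**What to change.** In the VAS part of section 4.3.2, keep Emax for the other 14 items. For *concentration* and *thinking*, add two summaries per session:

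- largest decrease = Emin minus the 0-min rating of that session;
- largest increase = Emax minus the 0-min rating of that session.

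Compare both between MDMA and placebo within subjects. Both directions are needed because the protocol states none, and a decrease-only score would fail in the same way if self-rated concentration rose. The same sentence should say whether the 0-min rating counts towards Emax and Emin.

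The cost is a sentence or two of text, one extra summary for two items and the noise of a single predose rating. No new data are needed. Fixing this before unblinding avoids choosing a direction after the results are seen.

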### **Facial emotion recognition task (FERT)**

The FERT is used to assess recognition of basic emotions. The FERT was sensitive to the effects of other psychoactive substances like MDMA [40, 41, 53, 64].

The task includes 10 neutral faces and 160 faces that express one of four basic emotions (i.e., happiness, sadness, anger, and fear), with pictures morphed between 0% (neutral) and 100% in 10% steps. Two female and two male pictures are used for each of the four emotions. Stimuli are shown in random order for 500 ms and are then replaced by the rating screen where participants have to indicate the correct emotion. The outcome measure is accuracy (proportion correct). The test data is recorded on a computer and processed into scores for each emotion using an established matlab routine according to SOPs (clinical pharmacology, Orca DKF). Accuracy scores are then compared between treatments using ANOVAs for each score. The test is performed once during each of the two main visits and 2-2.5 h after MDMA/placebo administration.

### **Multifaceted Empathy Test (MET)**

The MET is a reliable and valid task to assess the cognitive and emotional aspects of empathy [41, 53, 65]. The MET has been shown to be sensitive to oxytocin and MDMA [67]. The computer-assisted test consists of 40 photographs that showed people in emotionally charged situations. To assess cognitive empathy, the participants are required to infer the mental state of the subject in each scene and indicate the correct mental state from a list of four responses.

Cognitive empathy is defined as the percentage of correct responses in the total responses. To measure emotional empathy, the subjects are asked to rate how much they are feeling for an individual in each scene (i.e., explicit emotional empathy) and how much they are aroused by each scene (i.e., implicit emotional empathy) on a 1-9 point scale. The latter rating provides an inherent additional assessment of emotional empathy, which is considered to reduce the likelihood of socially desirable answers. The three aspects of empathy are each tested with 20 stimuli with positive valence and 20 stimuli with negative valence, resulting in a total of 120 trials. The test requires about 15 minutes. The test data is recorded on a computer and processed into scores for each empathy subscale using an established matlab routine according to SOPs (clinical pharmacology, Orca DKF). Empathy ratings are then compared between treatments using ANOVAs for each score. The test is performed once during each of the two main visits and 2-2.5 h after MDMA/placebo administration.

#### **4.3.3. Telephone interview**

Based on previous studies experience no formal follow-up support is needed but we will perform a telephone interview. 3 days after the main visits, patient or healthy participant will receive a phone call to inquire for Adverse Events using:

- A. The List of complaints e.g. sleeping problems, dry mouth, dizziness, palpitation, tremor, nausea, headache, transient anxiety and concentrating difficulties.
- B. Adverse Events that are not recorded by the LC e.g. subjective signs of depressed mood, psychosomatic problems, psychological problems and any perceptual disturbance e.g. flash backs.

The schedule of events for a subject is shown on **table1**

|                                         |                                          | SCREENING
VISIT | VISIT 1
MDMA/PLACEBO | VISIT 2
MDMA/PLACEBO | TELEPHONE
INTERVIEW
1 and 2 |
|-----------------------------------------|------------------------------------------|--------------------|-------------------------|-------------------------|-----------------------------------|
| Informed consent & Eligibility criteria |                                          | x                  |                         |                         |                                   |
| Questionnaires / Examination     |                                          |                    |                         |                         |                                   |
| Medical history questionnaire           |                                          | x                  |                         |                         |                                   |
| General physical examination            |                                          | x                  |                         |                         |                                   |
| ECG / standardized blood pressure       |                                          | x                  |                         |                         |                                   |
| Psychiatric interview (DSM IV)          |                                          | x                  |                         |                         |                                   |
| Questionnaires                          | Short Form 36 Health Survey (SF 36)      | x                  |                         |                         |                                   |
|                                         | State Trait Anxiety Inventory (STAI G/S) | x (G)              | x(S)                    | x(S)                    |                                   |
|                                         | Toronto Alexythymia Scale (TAS 20)       | x                  |                         |                         |                                   |
|                                         | Becks Depression Inventory (BDI II)      | x                  |                         |                         |                                   |
|                                         | List of complaints (LC)                  |                    | x                       | x                       | x                                 |
|                                         | Visual analog scales (VAS)               |                    | x                       | x                       |                                   |
| Face emotion recognition (FERT)         |                                          |                    | x                       | x                       |                                   |
| Multifaceted empathy task (MET)         |                                          |                    | x                       | x                       |                                   |
| Clinical parameters              |                                          |                    |                         |                         |                                   |
| Blood pressure (mmHg)                   |                                          | x                  | x                       | x                       |                                   |
| Heart rate (bpm)                        |                                          | x                  | x                       | x                       |                                   |
| Body temperature (°C)                   |                                          | x                  | x                       | x                       |                                   |
| Weight (kg)                             |                                          | x                  |                         |                         |                                   |
| Height (cm)                             |                                          | x                  |                         |                         |                                   |
| Laboratory parameters            |                                          |                    |                         |                         |                                   |
| Red blood cell count                    |                                          | x                  |                         |                         |                                   |
| Haemoglobin (g/l)                       |                                          | x                  |                         |                         |                                   |
| Plasma sodium (mmol/l)                  |                                          | x                  | x                       | x                       |                                   |
| Plasma potassium (mmol/l)               |                                          | x                  |                         |                         |                                   |
| Plasma osmolality (mmol/kg)             |                                          | x                  |                         |                         |                                   |
| ALAT (U/l)                              |                                          | x                  |                         |                         |                                   |
| ASAT (U/l)                              |                                          | x                  |                         |                         |                                   |
| GGT (U/l)                               |                                          | x                  |                         |                         |                                   |
| Creatinine (umol/l)                     |                                          | x                  |                         |                         |                                   |
| eGFR (ml/min/1,73m2)                    |                                          | x                  |                         |                         |                                   |
| MDMA (pg/ml)                            |                                          |                    | x                       | x                       |                                   |
| Oxytocin (ng/ml)                        |                                          |                    | x                       | x                       |                                   |
| Copeptin (pmol/l)                       |                                          |                    | x                       | x                       |                                   |
| Cortisol (nmol/l)                       |                                          |                    | x                       | x                       |                                   |
| ACTH (pg/ml)                            |                                          |                    | x                       | x                       |                                   |
| Prolactin (mIU/l)                       |                                          |                    | x                       | x                       |                                   |
| TSH (mIU/l)                             |                                          |                    | x                       |                         |                                   |
| fT4 (pmol/l)                            |                                          |                    | x                       |                         |                                   |
| IGF1 (nmol/l)                           |                                          |                    | x                       |                         |                                   |

|                                                 |  |     |     |  |
|-------------------------------------------------|--|-----|-----|--|
| FSH (IU/l)                                      |  | x   |     |  |
| LH (IU/l)                                       |  | x   |     |  |
| Testosterone ♂ (nmol/l) / Oestradiol ♀ (pmol/l) |  | x   |     |  |
| Urine tests                                     |  |     |     |  |
| Pregnancy test (x)                              |  | (x) | (x) |  |
| Drug screening                                  |  | x   | x   |  |

The schedule of session for a subject is shown on **table 2**

|                                   | - 60 min | 0 min | 30 min | 60 min | 90 min | 120 min | 150 min | 180 min | 210 min | 240 min | 270 min | 300 min | 330 min | 360 min |
|-----------------------------------|----------|-------|--------|--------|--------|---------|---------|---------|---------|---------|---------|---------|---------|---------|
| Short medical questionnaire       | x        |       |        |        |        |         |         |         |         |         |         |         |         |         |
| Autonomic measurements     |          |       |        |        |        |         |         |         |         |         |         |         |         |         |
| Blood pressure (mmHg)             | x        | x     | x      | x      | x      | x       | x       | x       | x       | x       | x       | x       | x       | x       |
| Heart rate (bpm)                  | x        | x     | x      | x      | x      | x       | x       | x       | x       | x       | x       | x       | x       | x       |
| Body temperature (°C)             | x        | x     | x      | x      | x      | x       | x       | x       | x       | x       | x       | x       | x       | x       |
| Laboratory parameters      |          |       |        |        |        |         |         |         |         |         |         |         |         |         |
| Oxytocin (ng/ml)                  |          | x     |        |        | x      | x       | x       | x       |         |         |         | x       |         |         |
| MDMA (pg/ml)                      |          | x     |        |        | x      | x       | x       | x       |         |         |         | x       |         |         |
| Copeptin (pmol/l)                 |          | x     |        |        | x      |         | x       |         |         |         |         | x       |         |         |
| Serum cortisol (mmol/l)           |          | x     |        |        | x      |         | x       |         |         |         |         | x       |         |         |
| Prolactin (umol/l)                |          | x     |        |        | x      |         | x       |         |         |         |         | x       |         |         |
| ACTH (mmol/l)                     |          | x     |        |        | x      |         | x       |         |         |         |         | x       |         |         |
| Plasma sodium (mmol/l)            |          | x     |        |        | x      | x       | x       | x       |         |         |         | x       |         |         |
| Screening                  |          |       |        |        |        |         |         |         |         |         |         |         |         |         |
| Drug                              | x        |       |        |        |        |         |         |         |         |         |         |         |         |         |
| Pregnancy                         | x        |       |        |        |        |         |         |         |         |         |         |         |         |         |
| Psychopathological ratings |          |       |        |        |        |         |         |         |         |         |         |         |         |         |
| Face emotion recognition (FERT)   |          |       |        |        |        |         | x       |         |         |         |         |         |         |         |
| Multifaceted empathy task (MET)   |          |       |        |        |        |         | x       |         |         |         |         |         |         |         |
| Questionnaires             |          |       |        |        |        |         |         |         |         |         |         |         |         |         |
| VAS                               |          | x     | x      | x      | x      | x       | x       | x       |         | x       |         | x       |         | x       |
| STAI - S                          |          | x     |        |        |        |         |         | x       |         |         |         |         |         |         |
| LC                                |          | x     |        |        |        |         |         |         |         |         |         |         |         | x       |
| Food                       |          |       |        |        |        |         |         |         |         |         |         |         |         |         |
| Standardized Lunch/Breakfast      | x        |       |        |        |        |         |         | x       |         |         |         |         |         |         |

